##### Pre- and post-implementation

Several information on residents agreeing to participate in the implementation phase will be collected during the pre-implementation phase. Information include sex, age, ability to walk independently, with assistance, or wheelchair bound, and the Mini Mental State Examination test (MMSE) [51] to assess the progression of the dementia disease. The MMSE is the most frequent and globally used instrument, takes 5–10 min to administer and is tested for its reliability and validity [52, 53].

The Neuropsychiatric Inventory Nursing Home version (NPI-NH) will in the study be used to evaluate the effect of the intervention on PwD’s BPSD symptoms. This instrument is currently the most used and recommended tool for people living in nursing homes [54], it has been previously validated and has been established in several languages [55]. NPI-NH is developed to assess neuropsychiatric symptoms (BPSD) in people with mild, moderate, and severe dementia by care providers through a retrospective and semi-structured interview. The instrument consists of 12 different symptoms common in PwD: hallucinations, delusions, depression/dysphoria, anxiety, agitation/aggression, elation/euphoria, disinhibition, irritability/lability, apathy/indifference, aberrant motor behavior, appetite/eating change, and nighttime disturbances. First, a screening question is asked to determine if the 12 behavioral changes are present or absent, if changes are present, probing questions are assessed related to frequency of the behavior, severity, and how much the behavior is disturbing for the care provider [55]. Additionally, information on participants’ medication use is registered. The questions will be asked by a trained researcher interviewing each care professional identified as the primary care provider for the participating PwD. The interview sessions will be conducted as part of the daily work in the nursing home. The sessions will be delivered pre-implementation in March 2023 and post-implementation in May 2023. Reason for the short timeframe between pre- and post-implementation is because it is expected that participants’ dementia is progressing rapidly since most participants have severe dementia. Whereas the pre- and post-intervention evaluation does not require such short timeframe since the data collection is designed as repeated cross sectional.

#### Process evaluation

The aim of the process evaluation is to evaluate how the intervention has been implemented [56]. In the pre-and post intervention phase, interviews will be conducted with selected co-design team members. The interviews are designed as two focus group interviews, one including care staff and the other including relatives and volunteers. No interviews are done with residents, based on recommendation from the nursing home, due to their severe dementia. The first focus group interview will focus on the different experienced challenges before the co-design process, and the expectations for the coming development of the garden. The second focus group interview will provide insights into the development and implementation of the garden, experienced acceptability, appreciation, and appropriation of the garden design and intervention. The focus groups will be conducted locally at the nursing home and will be audio-recorded. An interview guide will be used to guide the semi-structured interviews based on the ‘Normalization Process Theory’ of implementation (see additional file 3). This theory focuses on four factors relevant for successful implementation: Coherence, Cognitive participation, Collective action, and Reflexive monitoring [57]. Two semi-structured single interviews will additionally be conducted with the nursing home manager and activity coordinator pre- and post-intervention to assess organizational challenges, staff attitude and physical challenges. The interview guide for the single interviews are based on the same framework by Grant et al. presented in the pre-intervention phase, called ‘The Garden-Use Model’ [36] (see additional file 1). During the co-design phase, field notes will be collected by one research team member not participating in the co-design workshops, to gain an understanding of the context and the co-design process explored, as well as challenges in co-designing with PwD. The filed notes will be guided by the Normalization Process Theory already presented (see additional file 3).

### Data analysis

#### Effect evaluation analysis

##### Pre- and post-intervention

The systematic camera observations will provide information on how many people are using the garden and which parts of the garden they are using before and after the intervention, 24/7 and for a whole month. This will provide information on whether more people are using the garden after the intervention and if they are using the renovated parts of the garden. As the camera is taking four pictures per hour, the amount of data at the end of each data collection will be 20,160 blurred pictures. For each picture, the cloud-based software platform will provide the number of people in the picture, which will be a data point in the dataset. Consequently, the dataset will consist of 20,160 datapoints sorted by date at baseline and the same amount again at follow up. The blurred pictures are used to identify which areas of the garden are being used. The garden will be divided into several zones and each zone will be given a number. A student assistant will go through all pictures and classify in which zones people are observed and how many people are observed in the zones. The differences between pre- and post-intervention observation data will be analyzed as repeated cross-sectional measures as person identification is not possible.

The collected survey data on staff burnout and use of the garden completed by staff, will be uploaded into the statistical software IBM SPSS Statistics version 28. The differences between pre- and post-intervention will be analyzed as repeated measures comparing the degree of job satisfaction, use of garden, and attitude towards use of garden. This will provide information on whether the intervention has decreased staff burnout and has changed their use of the garden and their attitude towards using the garden in the daily care of PwD.

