##### Pre- and post-intervention

Systematic observations are conducted using a camera solution called HallMonitor developed by Webitall Aps [44]. The HallMonitor-system uses a cloud-based software platform and a number of cameras mounted on the wall. Each camera unit is configured to take a picture every half hour within a specified time-period, for example, from 6 am to 11 pm. HallMonitor uses a GDPR compliant design in which the camera takes a picture and immediately sends it through an encrypted 3G or 4G connection to a cloud-based platform storage which only Webitall has access to. The original picture is deleted from the camera unit after it has been sent to the platform. An automated script on the software platform processes the pictures automatically through a neutral network, which counts all the people in each picture whereafter the picture is being blurred. This process takes less than 10 min to complete. The unit has its own cellular data connection and only requires power to operate, making it easy to use in different settings. The camera system is so far mainly used by municipalities and sports associations to collect data on how different sports facilities are used by the public. This will be the first time that the system is used within nursing homes. Camera observations will be done for one month during August 2022 (pre-intervention), and at the same time one year later (August 2023) during post-intervention to systematically assess whether the intervention will increase the use of the garden. Cameras are placed to collect data from 6 am in the morning until midnight for 30 days, taking a momentary picture every 15 min. Four cameras are placed inside the nursing home, facing out into the garden, and one camera is placed inside the green house, to ensure that the whole garden is captured on camera. Additionally, one camera is placed on each balcony facing the garden, to detect any use of the balcony to get into the garden, giving a total of six cameras. The compiled data makes it possible to determine the number of users at different times and days of the week and month, as well as assess which parts of the garden are being used.

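### Garden cameras: each 15-minute picture is the stated data point, with no allowance for people staying across pictures or for shared day effects; analysed that way, the change in garden use would look more precise than it is

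*Protocol article*

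**What the plan says.** Under Effect evaluation, Pre- and post-intervention, the cameras record "from 6 am in the morning until midnight for 30 days, taking a momentary picture every 15 min", in August 2022 and again in August 2023. Their stated purpose is to judge whether garden use rises. The camera total is given as six: four looking out from the building, one in the green house, and one on each garden-facing balcony. The balcony cameras are there "to detect any use of the balcony to get into the garden".

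Under Data analysis, Effect evaluation analysis, Pre- and post-intervention:

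- The unit: "the cloud-based software platform will provide the number of people in the picture, which will be a data point in the dataset".
- The amount: "Consequently, the dataset will consist of 20,160 datapoints sorted by date at baseline and the same amount again at follow up".
- The comparison: the pre-post "observation data will be analyzed as repeated cross-sectional measures as person identification is not possible".

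Neither section mentions serial correlation, clustering by day or camera, or aggregation. No test, model, standard error or interval is named for the camera data.

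**The concern.** Not being able to identify people explains why they cannot be linked from picture to picture or from year to year. It does not make the pictures independent. Anyone who stays longer than 15 minutes can be counted again in the next picture, and a visit of an hour adds to about four. A rainy day, a staff shortage or a summer party moves every picture of that day together.

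The information about a change between the two months is therefore less than the number of pictures suggests. If each picture counts as one observation, ordinary variation between days can look like a clear rise or fall. Increased garden use is a stated purpose of the programme, and the cameras are the objective measure of it.

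**Working it through.** **1. The plan's own count.** Pictures = hours per day × pictures per hour × days × cameras.

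- Recording plan (6 am to midnight = 18 h, every 15 min = 4 per hour, 30 days, 6 cameras): 18 × 4 × 30 × 6 = 12,960.
- With round-the-clock recording, as the analysis section has it ("before and after the intervention, 24/7 and for a whole month"): 24 × 4 × 30 × 6 = 17,280.
- Stated: 20,160. Over 17, 18 or 24 h, 2 or 4 pictures per hour, 28, 30 or 31 days and 1 to 12 cameras, it arises only as 24 × 4 × 30 × 7 or 18 × 4 × 28 × 10. Neither set of inputs is stated.

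The figure is not reproduced. The camera total needs clarifying too: 4 + 1 leaves one camera for the balconies, although the text puts one on each garden-facing balcony.

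**2. Overlapping stays, by formula.** With exponential stays of mean D minutes, counts 15 minutes apart correlate r = exp(−15/D). The true standard error exceeds the picture-level one by √[(1 + r)/(1 − r)].

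| Mean stay (assumed) | r | Factor |
|---|---|---|
| 10 min | 0.22 | 1.25 |
| 20 min | 0.47 | 1.67 |
| 30 min | 0.61 | 2.02 |
| 60 min | 0.78 | 2.84 |

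**3. Stays and day effects, by simulation.** Settings: no true change, one camera view, 72 pictures a day, 30 days per wave, on average one person in view, exponential stays, log-normal day effect, independent days, 600 runs per setting. The documents give no stay length, visit number or day variance, so these are assumptions.

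| Mean stay | Day-to-day log-SD | True SE / picture-level SE | Rejection, pictures | Rejection, daily means |
|---|---|---|---|---|
| 10 min | 0 | 1.20 | 10.2% | 3.2% |
| 10 min | 0.3 | 2.74 | 46.7% | 5.0% |
| 10 min | 0.6 | 4.81 | 67.0% | 4.8% |
| 20 min | 0 | 1.66 | 22.5% | 6.0% |
| 20 min | 0.3 | 2.93 | 51.3% | 4.8% |
| 20 min | 0.6 | 4.97 | 70.5% | 6.3% |
| 30 min | 0 | 2.00 | 33.2% | 5.8% |
| 30 min | 0.3 | 3.00 | 52.3% | 4.2% |
| 30 min | 0.6 | 4.85 | 69.5% | 5.2% |
| 60 min | 0 | 2.84 | 49.2% | 4.7% |
| 60 min | 0.3 | 3.49 | 58.0% | 5.7% |
| 60 min | 0.6 | 5.31 | 71.8% | 5.8% |

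The rows without day variation agree with step 2. A differently built simulation (20 visits a day, gamma-Poisson daily visits, geometric stays, 1,000 runs) gave picture-level rejection of 34.5% (mean stay 30 min, CV 0.3), 48.2% (30 min, CV 0.5) and 57.5% (60 min, CV 0.5). Daily totals gave 4.2% to 4.7%.

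**4. Effective number of pictures.** Six cameras give m = 72 × 6 = 432 pictures a day. The design effect is 1 + (m − 1) × ICC. For ICC 0.005, 0.01, 0.05 and 0.1 (assumed) it is 3.16, 5.31, 22.55 and 44.1. The 12,960 pictures then carry about 4,100, 2,440, 575 and 294 independent ones.

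**The case against.** The strongest reply is that the article names no test, standard error or interval for these data and never says that pictures are independent. A data point in a file sorted by date can be read as a description of the raw data. The measurement section speaks of users by time and by day, which leaves room for aggregation. A fuller analysis plan could use daily totals or clustered errors, and the study calls itself exploratory. This reply stands in part: a reader might infer that the error bars are already wrong, and the documents do not support that. What remains is that the article fixes the picture as the data point, names a cross-sectional comparison, and gives a reason that does not address dependence.

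The size is also open to challenge. With 10-minute stays and no day variation the factor is only 1.2. A reader might also conclude that the effective sample is simply 30 days per wave. Under step 4 that would need an ICC of 1 (12,960 / 432 = 30), so it is not established. The day is a safe unit of analysis, which is a different statement.

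On the balconies, a reader might infer that their counts will be added to garden use. No section says so. The balcony cameras have a purpose of their own, and pictures are to be classified by zone. What can be said is that most balconies have a dining table and seating, so presence there need not be garden use, and the article does not say how the two are kept apart.

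**Conclusion.** The point holds in conditional form. The stated data structure ignores dependence within stays and within days, and following it literally would overstate precision. The standard error of the change would be too small by roughly 1.2 to 3 times from stays alone, and by about 2.7 to 5 times with day-to-day log-SD of 0.3 to 0.6. Rejection with no true change would be about 10% to 72% at a nominal 5%, against about 3% to 6% for daily means. The direction is secure unless stays are very short and days hardly differ. The size rests on assumed stay length, visit number and day variation.

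Exploratory status excuses the missing sample size calculation, but it does not make overstated precision acceptable. Separately, 20,160 and the round-the-clock wording do not agree with the recording plan.

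**What to change.** - State that the unit for the camera comparison is the day, for example persons counted per valid picture per day, about 30 versus 30. Use the zone-day for zones. Keeping pictures as rows is equally acceptable with day-clustered or autocorrelation-robust standard errors. If weather spells link neighbouring days, allow for that as well, because the simulation took days as independent.
- Use picture-level data for descriptive plots by hour.
- Report balcony cameras separately from garden and green house cameras.
- Reconcile the recording hours, the number of cameras and the picture count between the measurement and analysis sections.
- State that a valid standard error still does not remove differences between two single Augusts, such as weather or occupancy, since there is no control garden.

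The cost is analysis wording only, with no new data. The price is that the stated precision becomes less favourable.

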##### Pre- and post-implementation

The completed NPI-NH instrument will be converted into a scoring sheet which will provide a score on four different parameters for each of the 12 behavioral symptoms. These four parameters are: 1) frequency; 2) severity; 3) overall score for the domain (frequency x severity); 4) work disturbances for staff. An overall score is being calculated by adding up the 12 behavioral symptoms. The score on work disturbances is not included but will be calculated separately as an overall score on work disturbances, by adding up the scores for the 12 behavioral symptoms. The collected information on medication use is combined with the NPI-NH scores for each participant. The differences between pre- and post-implementation will be analyzed as repeated measures to assess any positive or negative change in BPSD-symptoms, work disturbances and medication use for the intervention group and control group and their respective primary care provider.

This is a real-world quasi-experimental study assessing the implementation of an activity to improve certain health outcomes. As this is a single-case exploratory study, sample size calculations are not applicable. The number of participants is all residents of the nursing home and their care staff. We do not expect generalizable results, but focus on the exploration of implementation.

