### The case: nursing home for PwD

Recruitment of the nursing home was based on an invitation which was sent out to three nursing homes in Denmark. The nursing homes were invited as (1) only PwD resided there, (2) they were of acceptable size to enable effect analyses, and (3) their gardens seemed well designed to be used by PwD. The final nursing home included in this study was the only nursing home who answered the invitation with reasons related to issues with low garden-use, despite having a well-designed garden. The purpose was not to re-design a nursing home garden, but to gain knowledge on how low-cost design solutions can support a nature-based palliative rehabilitation program to improve heath and increase use of the garden at existing nursing homes challenged in using their gardens.

The intervention study takes place in a nursing home specifically for PwD, located in the southern part of Denmark. The nursing home has 52 residents with severe dementia living in small one-bedroom apartments including own bathroom and own kitchenette. Residents are allowed to keep pets in their apartment. The apartments are spread over three floors and assembled into smaller units with 8–9 residents in each unit, and a larger common area including a dining area, a kitchen, a living room, and smaller seating areas with windows overlooking either the garden or the parking lot. Half of the apartments are facing the garden and the other half are facing the parking lot. Meaning, that only half of the residents can see the garden from their apartment, whereas the other half can see the garden from the common area. Each unit has two balconies, one smaller facing the parking lot and one larger facing the garden. The balconies facing the garden each have an elevator which leads the residents to the garden at ground floor. The only access to the garden is through this elevator. Staff offices, meeting rooms, and larger kitchen are all placed at ground floor.

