The nursing home has 75 care staff working on day-, evening- and night shifts. The staff consists mainly of health care workers and health care assistants, but also a few pedagogues and nurses. No occupational therapist or physiotherapist are working at the nursing home. One health care worker is working as an activity coordinator, planning different activities such as summer parties, walking trips, social dog visits. The nursing home also uses volunteers to help initiate activities with some of the residents. The staff has on average 18 sick leave days per year.

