#### Implementation phase

During this phase, the new garden design is implemented. To ensure the staff's interest in garden activities in a broader sense and their willingness to accept responsibilities, a garden team is formed among them. The care staff is extremely important to involve and inform throughout the project period, as it is this group that, after completing the project, must ensure the continued use of the garden through meaningful activities.

Integrating garden activities into the nursing home's culture is one of the objectives of the implementation phase. Staff of three out of the six units at the nursing home will be required to facilitate garden activities for all residents at the three units two times a week for one month. Care staff will be asked to talk about practical experiences in the garden as they accumulate greater expertise throughout the implementation period. As a result, they become better at facilitating garden activities, and the new knowledge may become a part of their professional identities. The co-design group will simultaneously evaluate the tested garden activities, and a yearly cycle of events is planned for the PwD, their relatives, and staff members during all the seasons and special occasions. The project will require the creation of brief activity descriptions (idea cards), and examples of how staff and PwD might contribute to various activities must be described. The purchase of supplementary equipment (pruning shears, warm blankets, firewood, plant tables, pots, flower seeds, etc.) will enable the staff to begin garden activities with the PwD. The co-design team and staff will attend a follow-up workshop to discuss how gardening activities can be practically incorporated into daily care and fulfill the needs of PwD, especially those related to BPSD.

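### The garden programme is assigned by whole unit, but resident outcomes are to be analysed per participant as pre/post change in each group, with no unit effect and no stated between-group difference

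*Protocol article*

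**What the plan says.** All references are to the Protocol article.

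- **Assignment.** Under Implementation phase: "Staff of three out of the six units at the nursing home will be required to facilitate garden activities for all residents" of those units, twice a week for one month. The case description gives the layout: "The nursing home has 52 residents with severe dementia", in apartments "assembled into smaller units with 8–9 residents in each unit".
- **Measurement.** Under Effect evaluation, Pre- and post-implementation, NPI-NH is collected in March and May 2023 by a researcher "interviewing each care professional identified as the primary care provider for the participating PwD". The interval is kept short because rapid progression of dementia is expected.
- **Analysis.** Under Data analysis, Pre- and post-implementation, the data are held per person: "The collected information on medication use is combined with the NPI-NH scores for each participant". The planned comparison is described as follows: "The differences between pre- and post-implementation will be analyzed as repeated measures to assess any positive or negative change in BPSD-symptoms". The same sentence also covers the staff disturbance score and medicines, and it refers to both an intervention and a control group. No unit term is mentioned, no difference in change between the groups is written, and the units that form the control group are not named.
- **Ambition.** The same section calls the study single-case and exploratory, regards sample size calculation as not applicable, and expects no generalisable results.

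**The concern.** There are two linked problems.

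**The contrast.** A control group exists, but the sentence on analysis asks for change in each group, not for the difference between the groups. From March to May, residents move from late winter into spring and their dementia progresses. A change in the programme units alone cannot be attributed to the programme. Worsening in both groups, or improvement in both, would be uninformative without the comparison.

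**The unit of analysis.** Residents of one unit share staff, common rooms and delivery of the programme. Repeated measures handles correlation within a resident over time. It does not by itself handle correlation between residents of the same unit. If the groups are compared resident by resident, a peculiarity of one unit (a staffing change, an infection, a disruptive resident) can appear as a programme effect with an interval that is too narrow. This outcome is the article's instrument for judging the effect on residents' symptoms.

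**Working it through.** The plan gives no power, SD, effect size or ICC for NPI-NH, so there is no stated figure to reproduce. The layout is consistent: 6 × 8 = 48 and 6 × 9 = 54, which brackets 52.

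**Inputs from the article:** 52 residents, 6 units, 3 units with the programme. Mean unit size m = 52/6 = 8.67.

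**Inferred:** the other three units are the controls, giving about 26 v 26 residents. Only residents who agree to take part contribute, so 52 is a ceiling. Fewer residents per unit would lower the design effect somewhat.

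**Assumed:** the unit ICC of the change score, over the range 0 to 0.20.

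**Formulas.** Design effect DE = 1 + (m − 1) × ICC. True SE divided by naive SE = √DE. Effective residents per group = 26/DE. At ICC 0.05, for example: DE = 1 + 7.67 × 0.05 = 1.38, √1.38 = 1.18, 26/1.38 = 18.8.

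**Simulation.** 40,000 null trials per ICC, units of 9, 9 and 8 in each group, two-sided 5% tests. An individual-level t-test on change is compared with a t-test on the three v three unit means (4 df).

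| Assumed ICC | DE | SE factor | Effective n per group | Type I error, individual level | Type I error, unit means |
|---|---|---|---|---|---|
| 0 | 1.00 | 1.00 | 26.0 | 4.9% | 4.8% |
| 0.02 | 1.15 | 1.07 | 22.5 | 6.7% | 4.9% |
| 0.05 | 1.38 | 1.18 | 18.8 | 9.6% | 5.1% |
| 0.10 | 1.77 | 1.33 | 14.7 | 14.1% | 4.8% |
| 0.20 | 2.53 | 1.59 | 10.3 | 22.9% | 5.0% |

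The approximation 2 × (1 − Φ(1.96/√DE)) gives 6.8%, 9.6%, 14.0% and 21.8% for the last four rows, which agrees with the simulation.

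**Scope.** These figures apply to a between-group comparison. They do not carry over directly to within-group change, although correlated changes within a unit would narrow those intervals too.

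**Raters.** The number of residents per carer is not stated. With one resident per carer there is no rater clustering. With an assumed 2 to 3 residents per carer and a rater ICC of 0.1 to 0.3, the SE factor from this source runs from √1.1 = 1.05 to √1.6 = 1.26.

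**The case against.** **The wording does not exclude a correct analysis.** A repeated-measures mixed model can carry a unit effect, and with group as a factor it yields the difference in change. Model terms are often left to an analysis plan that is not shown here. This stands in part: narrow intervals are a conditional result. But the article does state the level of the data and the comparison to be made, and following that text leads to per-participant change in each group. The sentence needs correcting whatever a further document contains.

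**The study is exploratory.** This lowers the severity. It does not remove the point, because an understated standard error misleads about this home as well.

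**The between-group contrast is no cure-all.** This is correct. Units are not said to be randomised, and staff across the home take part in the co-design phase. Accounting for clustering does not remove selection between units.

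The documents do not support two stronger readings:

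- A reader might infer that one carer rates several residents. The article says only that the primary care provider is interviewed. It also says "The nursing home has 75 care staff working on day-, evening- and night shifts"; 75/52 = 1.44 staff per resident, so one carer per resident is possible.
- A reader might take the phrase that the invited homes were chosen because "they were of acceptable size to enable effect analyses" as a claim of adequate power for three v three units. It is a criterion for inviting homes, and the article disclaims any sample size calculation.

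**Conclusion.** The point holds in a limited form. Assignment is by whole unit, the analysis as written is by participant within each group, and no between-group difference is stated. If the groups are compared without regard to unit, the standard error is too small for any positive unit ICC: by a factor of 1.07 to 1.59 for ICC 0.02 to 0.20, with a type I error of about 7% to 23%. At ICC 0 the individual-level test is valid.

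These sizes rest on an assumed ICC, on the non-programme units being the controls, and on nearly all residents taking part. Rater clustering is an open question and is not included in them. Given the exploratory framing, this is a should-fix point: an ambiguity in the stated analysis that is cheap to repair, not a defect that invalidates the study.

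**What to change.** In Data analysis, Pre- and post-implementation:

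1. Name the three non-programme units as the control group, if that is intended, and say how the programme units are chosen.
2. State the effect as the between-group difference in May NPI-NH total, adjusted for the March total. Do the same for the work-disturbance total, and give the analogous between-group contrast for medication use.
3. Account for unit, either by a random intercept with small-sample degrees of freedom or by comparing the six unit mean changes (4 df). Add a rater term only if carers rate more than one resident. With one resident per carer it cannot be separated from residual error in a single-follow-up model.
4. Treat within-group change as descriptive.
5. Report estimates with intervals as exploratory, and note that selection between units remains because units are not said to be randomised.

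**Cost.** A few lines of text and no new data. The price is wider intervals. Against a naive analysis with 50 df, a unit-level analysis with 4 df has a half-width larger by √DE × 2.776/2.009: about 1.4 times at ICC 0, 1.6 times at 0.05 and 2.2 times at 0.20. Baseline adjustment recovers some precision. Its variance relative to change scores is (1 − r²)/(2(1 − r)), which at an assumed March–May correlation of r = 0.6 is 0.64/0.80 = 0.80.
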